#### Basic characteristics

Participants’ demographic characteristics (e.g., sex, age, education, marital status, living arrangements, occupation, and socioeconomic status) and history of disease and medication use will be collected by the recruiters using the self-designed questionnaire. The basic MoCA score, Global Deterioration Scale (GDS), and Beck Depression Inventory (BDI) will be used to assess the corresponding characteristics. Baseline measurement will be completed before randomization.

#### Primary outcomes

Cognitive function will be measured using the MoCA scale, which is a cognitive screening instrument created and validated to detect MCI. MoCA is a brief (about 10 min) test evaluating visuospatial/executive functions, naming, verbal memory registration and learning, attention, abstraction, 5-min delayed verbal memory, and orientation with a total score of 0–30 (a higher score equals better function). The Chinese version of MoCA (Fuzhou version) will be applied to this trial with demonstrated good validity, reliability, and sensitivity in the population in Fuzhou city [29].

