**Methods:**

In this multicenter, parallel-group, double-blind, randomized controlled trial, 360 aMCI participants will be recruited from six subcenters and randomly assigned to the acupuncture group, sham acupuncture group, and control group. The acupuncture group will receive *TiaoshenYizhi* (TSYZ) acupuncture, the sham acupuncture group will use streitberger sham acupuncture, and the control group will only receive free health education. Participants in the two acupuncture groups will receive real acupuncture treatment or placebo acupuncture three times per week, 24 sessions over 8 consecutive weeks. The primary outcome will be global cognitive ability. Secondary outcomes will be a specific cognitive domain, including episodic memory and execution ability, electroencephalogram, and functional magnetic resonance imaging data. Outcomes will be measured at baseline and the fourth and eighth weeks after randomization. Repeated measurement analysis of variance and a mixed linear model will be used to observe the intervention effect.

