## Methods and analysis

### Study design

The design of this study is a randomized controlled trial, strictly following the Standard Protocol Items: Recommendations for Interventional Trials (SPIRIT) statement (see Additional file 1) [25]. The allocation will be hidden, and the allocation ratio will be 1:1:1. A total of 360 eligible participants will be randomly assigned to the TiaoshenYizhi acupuncture group, the sham acupuncture group, and the control group. Participants will be evaluated at baseline (weeks -2 to 0) and weeks four, eight, and 12. EEG will be used to explore the diagnostic value of event-related potential (ERP) in aMCI, and fMRI will be used to measure the structure and function of brain regions related to episodic memory at baseline and eight weeks. All data collectors will not know the group assignment. The research procedure and results evaluation schedule of this trial are shown in Fig. 1 and Table 1.

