### Study population

The study population will be community-based aMCI patients in Shenzhen, Fuzhou, Nanning, Nanjing, Bengbu, and Jiujiang city. The diagnostic, inclusion, and exclusion criteria of the study sample are as follows.

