### Randomization, allocation concealment, and blinding

After baseline evaluation, the eligible participants will be randomly divided into the TiaoshenYizhi acupuncture group, sham acupuncture group, and control group. The randomly assigned sequences will be generated using the online randomization tool MedSci (http://tools.medsci.cn/rand) and managed by independent statisticians who are not involved in the recruitment, evaluation, and intervention of participants. The independent research assistant will inform eligible participants of their allocation results by telephone. We could not establish the blinding of participants, acupuncturists, or intervention supervisors to the assigned treatment, but result evaluators and data statisticians will be blind to the grouping assignment.

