### Statistical analysis

Statistical analysis will be performed using SPSS software V.26.0 (IBM) package by an independent statistician, with a statistical significance of *P* value < 0.05 on both sides. Categorical variables will be described as frequencies or percentages using a chi-square test. For the normal distribution, continuous variables will be expressed using mean ± standard deviation (SD) and will be assessed by one-way analysis of variance (ANOVA) and compared between every group. For non-normal distribution, continuous variables will be expressed using the median and its interquartile range (IQR) and be analyzed by the rank sum test. The missing data will be filled in using the multiple imputation method. When baseline index imbalances occur among the three groups, a general linear model or logistic regression model will be applied for the calibration and analysis.

Adverse effects (AEs) will be analyzed using a Chi-square test or Fisher’s exact test. If the formal statistical analyses between groups cannot be performed due to the lack of power, AEs will be tabulated and summarized using descriptive statistics. For fMRI data, DPABI (a toolbox for Data Processing & Analysis for Brain Imaging, Version 2.3_170105, http://rfmri.org/dpabi) software package will be used to preprocess the image data obtained by fMRI scanning under the Matlab2013a (The Match Works, Inc). Independent component analysis (ICA) will be used to extract time signals for sequence dynamic causal modeling (DCM) analysis. Components will be extracted from the preprocessed images using GIFT v4.0 (http://icatb.sourceforge.net/).

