The characteristics of acupuncture treatment make it difficult to implement the double-blind method; therefore, we will blind participants by setting up the sham acupuncture group as a placebo [28, 50]. Considering the placebo effect of sham acupuncture, the health education group will be set up as a negative control group, providing prevention knowledge of common geriatric diseases, including AD. We increased the sample size and expanded the scope of the crowd compared with our previous research. The intervention can be implemented in community medical centers, and the adverse events can be fully evaluated. The main challenge of this study is whether such a large number of patients with aMCI are willing to receive acupuncture treatment until the end of the study and cooperate with the collection of each outcome. We will give material rewards to the participants.

In conclusion, through this study, the effectiveness of TiaoshenYizhi acupuncture on the episodic memory of patients with aMCI will be further clarified. We expect that this study will provide a reference for early treatment of aMCI and AD. The results of the study will be reported according to the guidance of the Consolidated Standards of Reporting Trials statement (STRICTA) [51].

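### Six-city trial: none of the analyses named for MoCA includes centre, and adjustment waits on observed baseline imbalance; this is a modest loss of precision, not a bias

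*Protocol article*

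**What the plan says.** Study population (Protocol article) defines the sample as "community-based aMCI patients in Shenzhen, Fuzhou, Nanning, Nanjing, Bengbu, and Jiujiang city". The abstract states that "360 aMCI participants will be recruited from six subcenters and randomly assigned" to three arms, and Study design adds that "the allocation ratio will be 1:1:1".

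Under Primary outcomes, "The Chinese version of MoCA (Fuzhou version) will be applied to this trial", and the support given for it is "with demonstrated good validity, reliability, and sensitivity in the population in Fuzhou city".

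On allocation, the article says: "The randomly assigned sequences will be generated using the online randomization tool MedSci". Independent statisticians manage the sequences. No stratum, block or centre is mentioned, and none is ruled out.

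On analysis, two places differ:

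- **Statistical analysis section:** normally distributed continuous variables "will be assessed by one-way analysis of variance (ANOVA) and compared between every group". A rank sum test is used otherwise. A general linear or logistic model comes in only when a baseline index turns out to be imbalanced.
- **Abstract, Methods:** the intervention effect is to be examined by repeated-measures ANOVA and a mixed linear model.

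Neither place names centre.

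**The concern.** Centre is a design variable, fixed for each participant before randomisation. Whether it enters the primary model can and should be decided in advance. The Statistical analysis section does more than stay silent. It commits to a test with arm as the only factor, and it makes any adjustment depend on what the baseline data show. Centre is not a baseline index in the ordinary sense, so that trigger may never bring it in.

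Two things follow if MoCA change differs between cities:

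- **Allocation not balanced by centre.** Between-centre variance stays in the residual, and chance differences in the centre mix add noise to the arm comparison.
- **Allocation stratified by centre in a document not shown.** The arm means are protected, but the residual is still too large, so the test is conservative.

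In both cases information is discarded. There is little slack: the planned difference in MoCA change is 5.50 − 4.88 = 0.62 points, with an SD of about 2.5.

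**Working it through.** **Inputs from the Sample size section.** Effect size f = 0.17, two-sided α = 0.05, power 80%, N = 300 before loss and 360 after. MoCA change is 5.50 (SD 2.48) and 4.88 (SD 2.45), so the pooled SD is √[(2.48² + 2.45²)/2] = 2.465.

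**Assumed.** The share of MoCA-change variance due to centre (ICC) is 0.01, 0.05 or 0.10, because the documents give no figure. The simulation takes six equal centres of 60, with 120 per arm.

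**Step 1: the plan's own figure.** For a three-group one-way ANOVA, the noncentrality is λ = N·f². At N = 300, λ = 300 × 0.17² = 8.67 on 2 and 297 degrees of freedom, which gives 75.0% power. Reaching 80% needs N = 339, so the stated 300 is not reproduced by this test. A three-group repeated-measures between-groups test gives 306 (two measurements) or 294 (three) if the correlation is taken as 0.8, but the article states neither input. Nor does 0.17 follow from the quoted means: 0.62/2.465 = 0.25, or f = 0.126 for two groups. Those are separate matters; f = 0.17 and N = 300 serve here only as a common yardstick.

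**Step 2: omitting centre.** Take 0.17 as the effect with centre variance removed. Leaving centre out multiplies the residual variance by 1/(1 − ICC), so λ becomes 8.67 × (1 − ICC).

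| ICC (assumed) | Residual variance | λ at N = 300 | Power at N = 300 | N for 80% |
|---|---|---|---|---|
| 0 | ×1.00 | 8.67 | 75.0% | 339 |
| 0.01 | ×1.01 | 8.58 | 74.5% | 342 |
| 0.05 | ×1.05 | 8.24 | 72.6% | 354 |
| 0.10 | ×1.11 | 7.80 | 70.1% | 375 |

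Spending five degrees of freedom on centre (denominator 292 rather than 297) leaves the 75.0% unchanged to one decimal.

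**Step 3: error rate and noise.** Simulation under no treatment effect, 8,000 runs per cell, analysed by one-way ANOVA:

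| ICC | Type I error, allocation not stratified | Type I error, stratified by centre | SD of centre-caused arm difference, not stratified |
|---|---|---|---|
| 0.01 | 4.9% | 4.7% | 0.012 × 2.465 = 0.03 points |
| 0.05 | 5.3% | 4.6% | 0.026 × 2.465 = 0.06 points |
| 0.10 | 5.1% | 3.9% | 0.037 × 2.465 = 0.09 points |

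The Monte Carlo standard error is √(0.05 × 0.95/8000) = 0.24 percentage points. The unstratified column is therefore compatible with 5%. In the stratified column only the 3.9% lies clearly below 5% by simulation alone, but the direction is as expected, since the residual is inflated while the arm contrast is not. With stratification, the centre-caused arm difference is zero.

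**The case against.** The best counter-argument is that this is a condensed article. Stratification factors and model covariates are commonly left to the full protocol or analysis plan, and a mixed linear model can carry centre. That stands for allocation: the article does not exclude stratification, so its silence is no ground for asking for new randomisation lists. Such a change would also alter the procedure mid-trial, with recruitment already under way (37 participants by August 2022). It does not dispose of the analysis point, because the Statistical analysis section positively names a single-factor test and a data-driven trigger. The one-way ANOVA is worded for continuous variables in general rather than for MoCA specifically, which is one more reason to reconcile it with the abstract.

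A second objection is size. Individual randomisation removes systematic bias, and the ordinary standard error already reflects chance imbalance. Stable city differences in MoCA level also largely cancel in change from baseline, which is the scale used for the sample size, so only differences in change matter. All of this stands and keeps the point modest.

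A reader might go further and infer that a MoCA version supported by Fuzhou data distorts the arm comparison in the other five cities. The documents do not support that. The same instrument is used in all three arms, so its validity elsewhere is a measurement question common to them, and a centre term would not answer it. Nor do the documents show that operators or assessors differ by city. They give no number of acupuncturists, describe the assessors only as experienced and blinded doctors, and say of the setting only that "The intervention can be implemented in community medical centers".

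**Conclusion.** The point holds as one of precision and prespecification. None of the named analyses includes centre, the two descriptions of the analysis do not agree, and adjustment is tied to observed imbalance. There is no systematic bias and no inflation of type I error.

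The cost of the omission is about 0.5 to 5 percentage points of power for an assumed ICC of 0.01 to 0.10, or mild conservatism if allocation is stratified. This rests on the assumed ICCs, on equal centres in the simulation, and on reading f = 0.17 as the effect with centre removed. If 0.17 already includes centre variance, the same comparison appears as power gained by adjusting rather than lost by not adjusting. If centres hardly differ in MoCA change, the gain is close to nil, but so is the cost of including the term.

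**What to change.** Reconcile the abstract and the Statistical analysis section into one named primary model for MoCA. Prespecify centre as a fixed factor in it for all participants, whatever the baseline comparison shows. The term should absorb centre differences in change. A main effect does this when the outcome is change from baseline or a follow-up score adjusted for baseline. If baseline MoCA is instead kept among the repeated outcomes, centre must be allowed to vary by visit.

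Report the treatment-by-centre estimates descriptively as a consistency check, not as a test on which the conclusion depends. If allocation is stratified by centre, say so in the same place.

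The cost is five degrees of freedom for the main effect (more if centre varies by visit) and one sentence. It needs no extra participants, and those already randomised are covered by the same term.

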#### Secondary outcomes

Episodic memory will be evaluated using the Auditory Verbal Learning Test-Huashan version (AVLT-H). AVLT-H assesses the short-term delayed free recall and the long-term delayed free recall, having good reliability and validity in evaluating episodic memory of patients with aMCI [30]. The participant will be asked to repeat learning a list of 12 words three times, with a short delayed recall after an interval of 3–5 min, and a long delayed recall, cue recall and identification after an interval of 20 min. The most sensitive evaluation index is the score of long delay recall and identification. The score of the AVLT-H will be expressed as a memory quotient (MQ), and the higher the MQ means better memory.

The execution function will be assessed using the Chinese version of Trail Making Test-B (TMT-B) [31, 32]. In TMT-B test, the participant will be asked to draw a line alternating between circles and squares according to the numbers in ascending order. The maximum time of completion for each participant is 300 s. Attention ability and short-term memory (STM) will be measured using the Digit Span Subtest (DSST) from the Wechsler Adult Intelligence Scale-IV.

Quality of life will be measured by the Medical Outcomes Study 36-Item Short-Form Health Survey (SF-36) [33]. It consists of 36 items assessing eight health concepts: functional capacity (10 items), physical activities (4 items), social activities (2 items), bodily pain (2 items), mental health (5 items), usual activities (4 items), vitality (4 items), and general health status (5 items) [34]. Each health concept is evaluated separately by the normalized scores of 0–100, with 0 corresponding to the worst health status and 100 corresponding to the best health status. The Chinese version of SF-36 has demonstrated high reliability and validity in the Chinese population [35, 36].

#### fMRI and EEG outcomes

The function of related brain regions will be measured using fMRI. The fMRI scan will be conducted in the medical imaging department of Rehabilitation Hospital Affiliated with Fujian University of Traditional Chinese Medicine. Siemens Prisma 3.0T MR scanner and Siemens 64-channel head and neck coil will be used for fMRI data acquisition. Scanning parameters are as follows:

High-resolution three-dimensional T1-weighted: TR = 2300 ms, TE = 2.27 ms, flip angle = 8°, slice thickness = 1.0 mm, FOV = 250 × 250 mm, matrix = 256 × 256, Voxel size = 0.98 × 0.98 × 1 mm^3^, and number of slices = 160.Resting fMRI: TR = 2000 ms, TE = 30 ms, flip angle = 90°, slice thickness = 3.6 mm, FOV = 230 × 230 mm, matrix = 64 × 64, voxel size = 3.6 × 3.6 × 3.6 mm^3^, number of slices = 37, axial slices = 35, and phases per location = 240.

EEG measurements will include different frequency bands (front α, α, β, δ, and θ) of spectral power and θ/α ratio. Receiver operating characteristic (ROC) analysis will be performed to evaluate the accuracy of EEG as a diagnostic indicator.

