#### Inclusion criteria

The eligible participants must meet the following criteria:

Participants meeting the diagnostic criteria of aMCI.Participants aged 55–75 years.The participants’ mother tongue will be Chinese, and they will have at least a primary school education.Participants will be right-handed.Participants who have subjectively ongoing memory decline or cognitive decline compared to their normal status within the last five years, as confirmed by their caregivers.Participants whose ability of daily living (ADL) remained normal with ADL scale (14-item table) scores being ≤ 18 points.Participants participate voluntarily and provide signed informed consent.

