### Outcome assessment

The variables in this trial consist of demographics and clinical characteristics, primary outcomes, and secondary outcomes. The basic characteristics will be measured at baseline (1–2 weeks before randomized allocation). Primary and secondary outcomes will be measured at baseline, the middle of intervention (4 weeks), the end of intervention (8 weeks), and 4 weeks of follow-up. Outcomes of fMRI and EEG will be measured at baseline and the end of intervention (8 weeks). All outcomes will be evaluated by experienced doctors who will be blinded to the allocation results of participants. A summary of all measurements in this trial is shown in Table 2.

**Table 2 Tab2:** Trial processes chart

Study period Item	Enrolment and Baseline	Intervention Period (8 weeks, one time per 4 weeks)				Follow-up phase
**Week**	-2 to 0	1 to 3	4	5 to 7	8	12

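### The planned diagnostic ROC analysis of EEG cannot be done: every participant has aMCI, so there are no non-cases

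*Protocol article*

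**What the plan says.** Two places in the protocol article give EEG a diagnostic role. Study design states: "EEG will be used to explore the diagnostic value of event-related potential (ERP) in aMCI". The section on fMRI and EEG outcomes adds: "Receiver operating characteristic (ROC) analysis will be performed to evaluate the accuracy of EEG as a diagnostic indicator". Neither names a reference standard or a comparison group.

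The population is described consistently as aMCI only:

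- Study population: "The study population will be community-based aMCI patients in Shenzhen, Fuzhou, Nanning, Nanjing, Bengbu, and Jiujiang city".
- Inclusion criteria, first item: "Participants meeting the diagnostic criteria of aMCI".
- Abstract, Methods: "360 aMCI participants will be recruited from six subcenters and randomly assigned to the acupuncture group, sham acupuncture group, and control group".

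The Control group section and the Discussion show that the third arm is a randomised arm given health education. In the Discussion's words, "the health education group will be set up as a negative control group". EEG is recorded at baseline and at week 8.

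On the marker itself, the outcome section says "EEG measurements will include different frequency bands" and goes on to spectral power in five named bands and the theta/alpha ratio. It mentions no event-related potential.

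**The concern.** An ROC curve plots sensitivity against one minus specificity. Sensitivity is estimated in people who have the target condition and specificity in people who do not, so both groups are needed. The target condition here is aMCI, and having it is a condition of entry. The word control does not help, because in this trial it denotes a treatment allocation and not freedom from disease.

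Two things are at stake. First, a stated analysis cannot be delivered. Second, a prespecified diagnostic ROC beside a group called control invites an analyst to use arm, or visit, as the binary state. That would yield an AUC, but one describing how well EEG separates treated from untreated patients, or before from after. Reported under the protocol's label, it could be taken for evidence of diagnostic accuracy.

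The mismatch in the marker adds to the problem. Event-related potentials and resting-type spectral measures are different index tests, and the protocol attaches the diagnostic aim to the first while mentioning only the second among the EEG outcomes.

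**Working it through.** The protocol gives no AUC, precision target or sample size for the ROC analysis, so there is no figure of its own to reproduce. The check is whether the quantities exist under the stated design.

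**Inputs**

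- Target condition: aMCI (Study design).
- Participants with aMCI: *m* = 360 (Abstract, Methods; Study design). This takes EEG to be recorded in all of them; a smaller *m* would not change the result.
- Participants without aMCI: *n* = 0 (Inclusion criteria; Study population; no other group is described anywhere in the article).

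**Step 1. Specificity.** Specificity = true negatives / *n* = 0/0, which is undefined at every cut-off.

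**Step 2. AUC.** The empirical AUC is the number of concordant case/non-case pairs divided by *m* × *n*. Here *m* × *n* = 360 × 0 = 0 pairs, so the AUC is undefined.

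**Step 3. Precision.** The Hanley–McNeil standard error for a true AUC of *A* is

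SE = √{[*A*(1 − *A*) + (*m* − 1)(*U* − *A*²) + (*n* − 1)(*V* − *A*²)] / (*m* × *n*)}, with *U* = *A*/(2 − *A*) and *V* = 2*A*²/(1 + *A*).

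With *n* = 0 the denominator is zero and no standard error exists. Sensitivity at a chosen cut-off could still be tabulated, but a curve for aMCI cannot be drawn.

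**Step 4. What a real comparison group would give.** The protocol plans none, so the numbers of non-cases below are assumptions. They are set beside 360 aMCI participants. For *A* = 0.8 and *n* = 60: *U* = 0.6667, *V* = 0.7111, numerator = 0.16 + 359 × 0.02667 + 59 × 0.07111 = 13.93, denominator = 360 × 60 = 21,600, SE = 0.0254, and the 95% half-width is 1.96 × 0.0254 = 0.050. The same formula gives:

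| Assumed non-cases | Half-width, AUC 0.7 | AUC 0.8 | AUC 0.9 |
|---|---|---|---|
| 0 (as planned) | undefined | undefined | undefined |
| 30 | 0.085 | 0.065 | 0.039 |
| 60 | 0.064 | 0.050 | 0.031 |
| 120 | 0.050 | 0.040 | 0.027 |

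**Step 5. Index test.** Study design names event-related potentials. The outcome section names band power and the theta/alpha ratio. No event-related paradigm or component appears in either place.

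**The case against.** The strongest reply is that the ROC sentence does not say which state is to be classified. The aMCI-versus-normal reading comes from joining it to Study design, where the phrase about diagnostic value in aMCI might be taken to mean discrimination among aMCI patients. An ROC against another binary state, such as MoCA response, would be computable. Further, EEG and MoCA are both repeated at week 8, and the Sample size section assumes mean MoCA gains of 5.50 and 4.88 points. Some participants might then no longer meet an MCI criterion, so the zero count is certain only at enrolment.

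The qualification about timing stands. The rest does not rescue the analysis. The article names no within-aMCI state, response definition, MoCA cut-off or remission endpoint for the ROC, and none of these would be diagnosis of aMCI. Nor can a statistical analysis plan supply people without aMCI to a trial that excludes them. A separate reference cohort might be described in a fuller protocol, but nothing here mentions one, and the study population is defined without it.

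Two other objections have some force. The wording on EEG measures is open-ended and the article is condensed, so the missing event-related measure is a secondary inconsistency and not proof that none is planned. And the diagnostic aim is peripheral: it is absent from the Objectives and the abstract, and it touches neither the primary outcome nor the treatment comparison.

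**Conclusion.** The concern holds. As written, the protocol plans an estimate of diagnostic accuracy for aMCI in a sample with 360 cases and 0 non-cases at enrolment, so specificity and AUC are undefined. This is a contradiction between a stated analysis and the stated population, not a detail left for later. It rests on two readings: that the diagnostic target is aMCI, as Study design says, and that no non-aMCI group exists outside this article. The consequence is confined to a secondary, exploratory use of EEG and does not reach the MoCA comparison. It should be corrected before EEG results are analysed or reported. The disagreement over the EEG marker is a lesser point that should be settled at the same time.

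**What to change.** Remove the diagnostic aim from Study design and the ROC sentence from the fMRI and EEG outcomes section. Keep EEG in the role the Objectives already give it, as a mechanism outcome: for example, the baseline-adjusted week-8 difference between TSYZ and sham acupuncture in one named measure. The theta/alpha ratio would serve because it is already listed, but the choice is the sponsor's.

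If an ROC is wanted, define it as exploratory prediction of a prespecified week-8 MoCA response from baseline EEG, and do not call it diagnostic. If the diagnostic aim itself is to stay, the protocol must describe a non-aMCI comparison group with its own EEG recordings, a reference standard and a justified size; Step 4 of the working shows the precision that different sizes would give.

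In every case, make the two sections name the same EEG measure.

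The first two options cost wording only, and the sponsor gives up a claim the design could not support. Because recruitment had begun (37 participants by 12 August 2022), the change should be recorded as a dated amendment. The third option costs additional participants and EEG recordings.

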### Objectives

The main purpose of this multicenter study is to verify the efficacy and safety of acupuncture treatment for episodic memory impairment in patients with aMCI through a randomized controlled trial and then explore its neuroimaging mechanism through functional magnetic resonance imaging (fMRI) and electroencephalogram (EEG).

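### The planned diagnostic ROC analysis of EEG has no non-cases: every participant has aMCI, so specificity and AUC for aMCI cannot be computed

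*Protocol article*

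**What the plan says.** The analysis is stated in the fMRI and EEG outcomes section of the protocol article, after a list of spectral band powers and the θ/α ratio: "Receiver operating characteristic (ROC) analysis will be performed to evaluate the accuracy of EEG as a diagnostic indicator". That sentence does not name the condition to be diagnosed. Study design does: "EEG will be used to explore the diagnostic value of event-related potential (ERP) in aMCI".

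Four places fix who is in the trial:

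- Study population: "The study population will be community-based aMCI patients in Shenzhen, Fuzhou, Nanning, Nanjing, Bengbu, and Jiujiang city".
- Inclusion criteria, first item: "Participants meeting the diagnostic criteria of aMCI".
- Abstract, Methods: "360 aMCI participants will be recruited from six subcenters and randomly assigned".
- Study design: "A total of 360 eligible participants will be randomly assigned to the TiaoshenYizhi acupuncture group, the sham acupuncture group, and the control group".

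The Discussion explains the control arm by the placebo effect of sham needling: "the health education group will be set up as a negative control group". Its members come from the same aMCI population.

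The Objectives give EEG a different purpose, which is to help explain how acupuncture acts. EEG is recorded at baseline and week 8 (Outcome assessment and Table 2). The abstract counts it among the secondary outcomes.

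**The concern.** A diagnostic ROC curve plots sensitivity against one minus specificity. It therefore needs people with the condition and people without it, classified by a reference standard that does not depend on the test. Here the reference standard is the entry criterion, so it takes the same value for everyone. The word control may hide this, because the control arm is a treatment control and supplies no disease-free subjects.

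As the plan stands, the analyst must either abandon a stated analysis or choose another label after the data are in. If a label is improvised, the resulting AUC would answer a different question, yet the wording in the plan invites reporting it as diagnostic accuracy for aMCI.

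**Working it through.** The plan gives no AUC, sensitivity, specificity or sample size for the ROC, so there is no figure to reproduce. The check is structural.

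**Inputs**

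| Item | Value | Source |
|---|---|---|
| Target condition | aMCI | Study design |
| Participants with aMCI | 360 | Abstract, Methods; Study design; Inclusion criteria |
| Participants without aMCI | 0 | Study population; Inclusion criteria |
| EEG visits | baseline, week 8 | Outcome assessment; Table 2 |
| Other binary reference state | none named | fMRI and EEG outcomes; Statistical analysis |

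**Step 1: specificity.** Specificity = TN / (TN + FP), and TN + FP is the number of non-aMCI participants. That number is 0, so the ratio is 0/0 and undefined.

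**Step 2: AUC.** AUC is the proportion of case/non-case pairs in which the case has the more abnormal score. The number of pairs is 360 × 0 = 0, so AUC is undefined.

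**Step 3: what remains.** Only sensitivity at a chosen cut-off could be estimated. Without specificity it says nothing about accuracy, since a cut-off that labels everyone positive has sensitivity 1.

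**Step 4: could non-cases come from elsewhere in the trial?**

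- *The control arm.* No. Its members meet the same entry criteria.
- *People who fail screening.* Under Recruitment, community doctors settle eligibility first, and consent and baseline assessment follow for those who qualify. A few people might be found ineligible after an EEG, but the plan does not describe them as a reference group.
- *Change of status by week 8.* Table 2 repeats the cognitive scales but schedules no second application of the aMCI diagnostic criteria, and no rule for a change of status is given.
- *Loss to follow-up.* It lowers the number of cases and leaves the number of non-cases at 0.

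**Step 5: is this a question of precision?** No. For illustration, suppose m non-cases had been enrolled beside the 360 cases. With Q1 = A/(2 − A) and Q2 = 2A²/(1 + A), the Hanley–McNeil standard error is

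SE = √{[A(1 − A) + 359(Q1 − A²) + (m − 1)(Q2 − A²)] / (360m)}.

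The 95% half-width, 1.96 × SE, is then:

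| Assumed AUC | m = 60 | m = 120 | m = 360 | m = 0 (as planned) |
|---|---|---|---|---|
| 0.7 | 0.064 | 0.050 | 0.038 | undefined |
| 0.8 | 0.050 | 0.040 | 0.032 | undefined |

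The AUC values and m are assumptions, not figures from the plan. Even a modest comparison group would give a usable estimate, but more aMCI patients never would.

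**The case against.** **The ROC sentence names no target, and the two statements on EEG concern different signals.** Study design speaks of event-related potentials, while the ROC sentence follows a list of spectral measures. This is fair as a reading of that sentence alone, and the index that enters the ROC should be made consistent. It does not rescue the analysis. Study design gives the only diagnostic target for EEG in the article, and the lack of non-cases is the same whichever signal is used.

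**The article condenses a fuller protocol.** A reference sample or another target state might be defined there. That cannot be excluded. But the point does not rest on a missing detail. A stated analysis conflicts with a stated population, and an analysis plan cannot supply participants whom the trial does not enrol. It could define another label within aMCI, but that would be a different question from the one now written.

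**The aim is exploratory.** This stands. The primary outcome and the sample size both rest on MoCA, and nothing here touches randomisation, safety monitoring or the estimate of the treatment effect.

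Two stronger readings are tempting and should be resisted:

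- *A reader might infer that the EEG data are not used for the treatment question, or that the randomised EEG contrast is absent from the plan.* The documents do not support this. The abstract lists EEG as a secondary outcome and gives repeated-measures ANOVA and a linear mixed model for the intervention effect, without excluding EEG. The Statistical analysis section gives general methods for continuous variables. What can be said is that ROC is the only analysis tied specifically to EEG.
- *A reader might infer that a curve could be drawn only by using arm or visit as the disease label.* That is not so. Another binary state within the trial, such as response on MoCA, would also yield a curve. The plan names none, and nothing in it proposes arm or visit.

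**Conclusion.** The diagnostic ROC analysis cannot be carried out in the trial described. There are 0 non-aMCI participants among 360, so specificity and AUC for diagnosing aMCI are undefined at any sample size. The conclusion rests on two readings of the article: that the condition to be diagnosed is aMCI, as Study design says, and that no comparison group exists outside the three randomised arms, since none is described.

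The severity is moderate. A stated analysis is wrong as written and could lead to a misdescribed AUC, but the loss is confined to an exploratory aim and leaves the primary MoCA comparison as it is.

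**What to change.** 1. In Study design, remove the aim of exploring the diagnostic value of EEG in aMCI.
2. In fMRI and EEG outcomes, remove the diagnostic ROC sentence. State instead that the EEG measures are compared between arms at week 8, adjusted for the baseline EEG value, and label this exploratory. Use the same EEG measures in both sections.
3. If an ROC is kept, name a binary reference state that exists within the trial, define it before the data are seen, and make no claim of diagnostic accuracy for aMCI. For example, baseline EEG could be assessed against MoCA response at week 8, which would need a stated threshold for response.

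This costs wording only, since EEG is already scheduled at baseline and week 8. The sponsor gives up a diagnostic claim that the design cannot support. Keeping that claim would require a non-aMCI reference group with its own EEG recordings, which means extra recruitment outside the randomised comparison.
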